## Abstract

**Background:**

Major depressive disorder (MDD) is a debilitating condition that affects more than 300 million people worldwide. Current treatments are based on a trial-and-error approach, and reliable biomarkers are needed for more informed and personalized treatment solutions. One of the potential biomarkers, gamma-frequency (30–80 Hz) brainwaves, are hypothesized to originate from the excitatory-inhibitory interaction between the pyramidal cells and interneurons. The imbalance between this interaction is described as a crucial pathological mechanism in neuropsychiatric conditions, including MDD, and the modulation of this pathological interaction has been investigated as a potential target. Previous studies attempted to induce gamma activity in the brain using rhythmic light and sound stimuli (GENUS – Gamma Entrainment Using Sensory stimuli) that resulted in neuroprotective effects in Alzheimer’s disease (AD) patients and animal models. Here, we investigate the antidepressant, cognitive, and electrophysiological effects of the novel light therapy approach using 40 Hz masked flickering light for patients diagnosed with MDD.

**Methods and design:**

Sixty patients with a current diagnosis of a major depressive episode will be enrolled in a randomized, double-blinded, placebo-controlled trial. The active treatment group will receive 40 Hz masked flickering light stimulation while the control group will receive continuous light matched in color temperature and brightness. Patients in both groups will get daily light treatment in their own homes and will attend four follow-up visits to assess the symptoms of depression, including depression severity measured by Hamilton Depression Rating Scale (HAM-D_17_), cognitive function, quality of life and sleep, and electroencephalographic changes. The primary endpoint is the mean change from baseline to week 6 in depression severity (HAM-D_6_ subscale) between the groups.

## Introduction

Major Depressive Disorder (MDD) is a common and serious medical illness characterized by often recurrent depressive episodes. While antidepressants and psychotherapy can be effective in managing the symptoms of depression, they fail to achieve remission in approximately one-third of individuals [1].

Currently, bright light therapy (BLT) is used for the treatment of seasonal depression. Although it has shown some effectiveness in non-seasonal MDD, the quality of the evidence is poor and a substantial rate of patients do not reach remission [2,3]. The reasons for this difference in effectiveness are not entirely clear, but BLT is known to affect mainly the circadian system by stimulating specific cells in the retina, suppressing melatonin production, and increasing serotonin levels [4]. Although the circadian system has profound effects on mood and general well-being, MDD is a more complex disorder with various genetic and environmental factors, brain regions, and neural networks contributing to its pathophysiology [5,6].

Depression affects multiple large-scale functional networks in the brain, with measures such as resting-state functional connectivity within the default mode network distinguishing depressed patients from healthy controls [7–10] or predicting response to specific antidepressant medications [11,12]. To address the problem of ineffective pharmacotherapy, various brain stimulation approaches, such as electroconvulsive therapy, transcranial magnetic or electrical stimulation, pulsed electromagnetic field therapy and deep brain stimulation, have been utilized or tested [13–16]. It is hypothesized that these therapies improve the symptoms of depression by modulating the brain at the network level.

Brain network activity could be modulated by various external stimuli, either magnetic, electrical or even auditory and visual [17]. For example, transcranial alternating current stimulation at 10 Hz has been investigated for the treatment of depression and hypothesized to improve clinical symptoms by renormalizing alpha oscillations in the left dorsolateral prefrontal cortex [18]. The brain can respond and synchronize to external sensory stimuli. Studies have shown that light flicker stimulus at specific frequencies can entrain the same frequency waves beyond the visual pathway in the hippocampus and prefrontal cortex [19–21]. Targeted activation of these regions could be beneficial for the integrity of structure and function of the underlying cells. For example, the hippocampus is a critical brain region responsible for memory and emotions [22,23], and the shrinking of the hippocampus is described in people with recurrent and poorly treated depressive episodes. A study using 3 months of 40 Hz daily stimulation on healthy elderly and AD patients has demonstrated lesser ventricular and hippocampal atrophy and better performance on face-name association delayed recall test [24]. This could indicate potential benefits and targeted approaches in patients with recurrent and difficult to treat depression.

In addition, intrinsic gamma activity measured by electroencephalography (EEG) or magnetoencephalography (MEG) is associated with higher cognitive functioning, information processing, and working memory [23,25]. Cognitive deficits occurring with depression have an essential role in treatment response and prognosis, and targeting the cognitive domain in depression could be a promising therapeutic approach [26,27]. Sensory stimulation with 40 Hz has not only been able to entrain gamma activity but increased the expression of brain-derived neurotrophic factor in mice [28], cleared up amyloid and tau proteins involved in Alzheimer’s disease (AD) rodent models [19,29–31], and improved mood, sleep, and daily functionality in patients with AD [31–33].

Even though the mechanisms behind gamma entrainment using sensory stimuli (GENUS) are not fully understood, considering the signs of hippocampal involvement and neuroprotective and cognitive effects associated with 40 Hz light stimulation, we want to investigate how this stimulation approach would affect brain network dysfunction and symptoms of depression. We hypothesize that daily 1-hour 40 Hz masked flickering light stimulation for 6 weeks can improve symptoms such as depressed mood, cognitive impairment, and disrupted circadian rhythms.

We aim to investigate the isolated effects of 40 Hz masked light by having a continuous color-temperature and brightness-matched light as a placebo comparator.

## Patients and methods

### Study participants

The study will recruit, in all, 60 males and non-pregnant females ages 18–75 with unipolar, non-psychotic MDD (according to DSM-5 criteria) who have a Major Depression Inventory (MDI) score of 21 or above and with a low risk of suicide (based on the Hamilton Depression Rating Scale item 3 suicidality question). Participants will be only included if they are on stable antidepressant medication and/or psychotherapy for at least two weeks before starting the trial and have no planned change of the medication regime for the 8 weeks study period. Only participants who are willing to comply with the scheduled plan and can use the device for one hour per day for 6 weeks will be included in the study.

The Mini International Neuropsychiatric Interview (M.I.N.I.) [34] will be administered to confirm the diagnosis of major depressive disorder and exclude co-existing conditions mentioned in the study protocol’s exclusion criteria. Scales regarding depression symptoms, suicidal ideation, sleep patterns, mania symptoms, and side effects will be recorded during the study visits.

Eligible patients will be recruited through outpatient clinics at Psychiatric Centre Copenhagen. Patients diagnosed with a major depressive episode will be recruited *via* their contact person at the outpatient mental health services. The contact person will ask patients if they are interested in being informed about the trial. If patients agree, a meeting between the participant and a study investigator will be scheduled. Patients will be assessed for eligibility based on inclusion and exclusion criteria predefined in the protocol. Informed consent will be obtained before the start of trial activities.

Patients with any history of seizures, photosensitive migraines, or eye disorders with light sensitivity will be excluded. The study aims to investigate the effects on unipolar, non-psychotic depression; therefore, patients with a known history of bipolar disorder or current psychotic symptoms will not be included in the investigation. The summary of all inclusion and exclusion criteria is provided in (Table 1).

**Table 1. t0001:** List of inclusion and exclusion criteria.

Inclusion	Exclusion
18–75 years Diagnosis of major depressive episode according to DSM-5 MDI score > 21 at screening Stable antidepressant medication and/or psychotherapy for at least two weeks before starting the trial. No planned change of antidepressant medication for the 8-weeks study period Willingness to comply with scheduled plan and using the device for 1 h per day for 42 days. Understanding the oral and written study information and willing to sign an informed consent.	History of photosensitive migraines and/or epileptic seizures Known eye disorders that might be sensitive to light treatment. Diagnosis of bipolar disorder according to DSM-5 criteria Suicidal ideation corresponding to a score of 2 or more on the HAM-D_17_ scale item 3 or if patient or investigator is uncertain of the degree of suicidal risk. Current psychotic symptoms. However, subjects with a prior psychotic depression or subjects with an actual psychotic depression episode that at time of informed consent no longer fulfils the psychosis criteria are allowed to participate. Current drug or alcohol dependence based on their medical records or the M.I.N.I. interview. Diagnosis of borderline personality disorder according to DSM-5 criteria Being enrolled in another investigational treatment study. Progressive neurodegenerative or neoplastic disease. Inability to understand the study procedures or handling of the NSS device. Pregnancy at time of inclusion or unsafe contraception in women of fertile age

Patients will receive standard of care therapy for their depression during the clinical trial. Only patients with any unforeseen changes in medication will be excluded from the study.

The study protocol was designed according to the Standard Protocol Items: Recommendations for Interventional Trials (SPIRIT) guidelines.

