**Figure 1. F0001:**
[figure not shown]
Visual representation of study design and follow-up visits. HAM-D_17_: Hamilton Depression Rating Scale 17 item version; MDI: Major Depression Inventory; WHO-5 World Health Organization Quality of Life Index; PSQI: Pittsburg Sleep Quality Index; SIDAS: Suicidal Ideation Assessment Scale; YMRS: Young Mania Rating Scale; UKU: The UKU Side Effect Rating Scale; SCIP: The Screen for Cognitive Impairment in Psychiatry. TMT-B: Trail Making Test Part B; FERT-Facial Emotion Recognition Task; ECMT: Emotional Categorization and Memory Test; SSVEPs: Steady State Visually Evoked Potentials.

Patients are free to withdraw from the trial at any time. Drop out criteria include hospitalisation due to a somatic illness, admission to a psychiatric ward for any length of time, side effects at a level unacceptable to the subject, worsening of depression such that it would be unethical not to try other treatments, the patient or the patient’s healthcare provider changes the dose of medication affecting the depression, onset of mania assessed according to the YMRS with a score of 7 or above or fulfilling the diagnostic DSM-5 criteria for a current hypomanic or manic episode, and patients reports conditions treatment that interfere with blinding. Patients who drop out from the trial continue their treatment and follow-up care at Psychiatric Centre Copenhagen.

A GCP monitor (GCP-Unit, University of Copenhagen, Frederiksberg Hospital) has been assigned to the study and will follow the clinical trial, randomization, blinding, and data collection procedures.

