### Data collection

Identifiable data such as full name, address, and social security number will only be shared with key personnel and only for data collection from the electronic patient journal. All data sharing will be according to the European General Data Protection Regulation (GDPPR) and in agreement with permission from the Danish data protection agency. The REDCap system is used for collecting data during patient visits. The only data collected outside of the investigational site is the average usage time of the device, which is stored locally on the device and does not include any personal information. Depression severity measures (HAM-D_17_) will also be collected from the patients that dropped out.

Data collected: Age, gender, social security number, e-mail, phone number, inclusion date, diagnosis, sociodemographic data (residential status, work situation, somatic condition, prior and current depressive episode, smoking, eliciting factors for depressive episodes, suicidality history, alcohol, drug abuse), medical history, depression, mania, quality of life, sleep, side-effect, and suicidality ratings, treatment expectancy, blinding and treatment evaluation, concomitant medication.

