### Statistical analysis plan

The analysis will be carried out using R software version 4.2.1 or higher (Free Software Foundation’s GNU General Public License). With a minimal clinically important difference of 3 points on the HAM-D_6_ scale, an expected standard deviation of 3.5, an alpha value of 0.05, and a power of 90%, and considering dropout, we will need a total of 60 patients to show the significance of the primary outcome. Based on the previous studies at Psychiatric Centre Copenhagen, dropout is expected to be below 25%, and we will attempt to administer the HAM-D_6_ (primary endpoint) for all the patients who drop out of the trial. An intention-to-treat population, including all randomized participants, will be used for analyses. The mean change from baseline to post-treatment at day 42 in HAM-D_6_ scores will be compared between treatment groups using a two-sample *t*-test. *T*-test assumptions of normality and equal variance will be checked. A mixed model repeated measures method will be used to analyze depression symptoms from baseline to measurements at day 7, day 21, day 42, and day 56. The Benjamini-Hochberg correction will be used for multiple comparisons. A *p*-value of less than 0.05 is considered a rejection of identity between groups.

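### The rule that a medication change gets a patient excluded from the study is at odds with the all-randomised analysis set, and the rating promised for drop-outs is not tied to day 42

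*Protocol article*

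**What the plan says.** All places are in the protocol article.

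- **Study participants, below Table 1.** "Patients will receive standard of care therapy for their depression during the clinical trial". The next sentence is "Only patients with any unforeseen changes in medication will be excluded from the study".
- **Table 1, inclusion criteria.** "No planned change of antidepressant medication for the 8-weeks study period". Eligibility therefore deals with planned changes only.
- **Study design and interventions, after Figure 1.** The drop-out criteria include the patient or provider making a change that "changes the dose of medication affecting the depression". They also include "worsening of depression such that it would be unethical not to try other treatments", admission to hospital or a psychiatric ward, unacceptable side effects, mania, and matters that interfere with blinding.
- **Data collection.** "Depression severity measures (HAM-D_17_) will also be collected from the patients that dropped out". No time point is given.
- **Statistical analysis plan.** "An intention-to-treat population, including all randomized participants, will be used for analyses". The section also promises an attempt at HAM-D6, labelled as the primary endpoint, in every patient who drops out. The primary test is a two-sample t-test on change from baseline to day 42.

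**The concern.** A change that nobody foresaw can only happen after enrolment, so the sentence below Table 1 is not an eligibility rule. Taken at its word, it takes randomised patients out of the study because of something that happened later. In patients with depression under usual care, a medication change is plausibly a reaction to how the patient is doing. That is an inference; the article does not say it. Worsening and psychiatric admission, both on the drop-out list, are tied to outcome more directly.

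Leaving such patients out of the primary comparison, or keeping them without a day-42 value, would mean that the two arms are no longer those that randomisation formed. If the active light works, more placebo patients would be expected to leave for poor response, and the remaining placebo patients would look better than their arm. If it harms, the reverse holds and harm could be masked.

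**Working it through.** **1. The sections side by side**

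| Question | Below Table 1 | Drop-out list | Data collection | Statistical section |
|---|---|---|---|---|
| Which medication change? | any unforeseen one | a dose change of medication that affects the depression | – | – |
| Other reasons to leave? | *only* this one, read literally | several | – | – |
| What follows? | exclusion from the study | drop-out | HAM-D still collected | HAM-D6 attempted; everyone randomised is analysed |
| When is the rating taken? | – | – | not stated | not stated for drop-outs; the primary test uses day 42 |

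Two mismatches are plain on the text. The triggers differ: a new drug for an unrelated illness meets the rule below Table 1 and not the drop-out criterion. Exclusion from the study and analysis of everyone randomised agree only if *excluded* means leaving trial procedures, and the article does not say that. The timing of the drop-out rating is a third, softer point.

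**2. Power with all patients, and with 25% lost**

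Inputs from the Statistical analysis plan: difference 3, SD 3.5, alpha 0.05 (two-sided assumed), power 90%, total 60, dropout below 25%. Allocation is 30 to 30 (Study design and interventions).

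Size per arm, normal approximation: n = 2(1.960 + 1.282)² × (3.5/3)² = 28.6, so 29 per arm or 58 in all. The t-test needs 29.6, so 30 per arm or 60. The stated 60 therefore matches 90% power with essentially no allowance for loss.

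Power ≈ Φ(3 / (3.5 × √(2/n)) − 1.960):

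- 60 analysed, n = 30: Φ(3.320 − 1.960) = 91.3%; exact t-test 90.4%.
- 45 analysed (60 × 0.75), n = 22.5: Φ(2.875 − 1.960) = 82.0%; exact t-test 80.2%.

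Both figures assume the true difference stays at 3, that is, loss without bias.

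**3. Bias, as illustration only**

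The removal mechanism is an assumption; the documents give none. Take a true difference of 3 and SD 3.5 in each arm.

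*Removal by day-42 change, one threshold c for both arms.* The mean of those kept is μ − 3.5 × φ(k)/Φ(k), with k = (c − μ)/3.5.

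| Removed overall | Active removed | Placebo removed | Expected difference |
|---|---|---|---|
| 5% | 1.3% | 8.7% | 2.5 |
| 10% | 3.4% | 16.6% | 2.2 |
| 25% | 12.2% | 37.8% | 1.7 |

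*Removal of the worst 15% to 25% at day 21*, assuming a day-21 effect of 1 to 2 points and a correlation of 0.5 to 0.7 with day 42: removal is 18% to 34% on placebo and 9% to 20% on active, and the expected difference is 2.4 to 2.8.

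The direction is the same under both rules, towards no difference. The size runs from about 0.2 to 1.3 points, depending wholly on the assumed mechanism and the share removed.

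**The case against.** The strongest reply is that the sections fit together. Read *excluded from the study* as dropping out of trial procedures. The drop-out list then covers nearly the same event, the outcome is still sought, and the patient stays in the analysis set. Only the statistical section defines an analysis population, and it keeps everyone. This stands: a reader might infer that the plan removes these patients from the analysis, or that the sections cannot all hold, and the documents support neither.

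The word *only* may also be mere contrast with the sentence before it (usual care goes on, and only a medication change leads to exit) and not a complete list of exits. That is a fair reading. The difference in the medication trigger remains.

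On timing, Table 3 ties the primary endpoint to baseline and day 42, so a promise to obtain the primary endpoint from drop-outs can be read as a day-42 rating. Detailed rules may also sit in a full protocol or analysis plan that is not shown, and their absence from a condensed article is no fault. The point therefore does not rest on missing rules. It rests on a stated exclusion rule that pulls against the stated analysis set.

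Finally, the 25% is an upper bound on dropout from all causes and not a rate of medication change. The bias figures describe an analysis without the removed patients, which the article does not plan. With no true effect, a rule acting on response alike in both arms would not by itself create a false positive. All of this stands.

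**Conclusion.** The point holds as a conflict of wording with possible consequences for the primary comparison. Taken literally, the sentence below Table 1 is a post-randomisation exclusion that disagrees with the intention-to-treat population, and its scope does not match the drop-out list. The rating promised for drop-outs is not expressly scheduled at day 42. It is not shown that any patient will be left out of the analysis.

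The size is conditional. At the stated inputs and two-sided 5%, t-test power is about 90% with 60 analysed and about 80% with 45. The second figure takes the plan's all-cause bound as fully reached and every such patient as lost to the primary test. If the loss were related to response there would also be bias, but no single figure for it can be drawn from the documents. The point merits correction because the remedy is cheap and a day-42 score that was not taken cannot be recovered later.

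**What to change.** Reconcile the four sections (Study participants, the drop-out criteria, Data collection, Statistical analysis plan):

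1. Reword the sentence below Table 1, and use one description of the medication trigger in both places. State that a medication change, or any other listed drop-out event, does not by itself end outcome follow-up or remove the patient from the intention-to-treat analysis. Which trigger applies, and whether and when device treatment stops, is for the sponsor to settle.
2. State that the HAM-D6 already promised for drop-outs is taken at the patient's scheduled day-42 date, by telephone if needed.
3. State that this value is analysed in the randomised arm whatever medication change has occurred.
4. Report medication changes by arm.

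The cost is a clarification of the text and a few ratings that are already promised in principle. The small downside is that medication changes made before day 42 may dilute the difference between the arms; the report by arm lets a reader judge how far.

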## Study design and interventions

The study is a randomized, double-blinded, placebo-controlled, single-center clinical trial investigating the effects of 40 Hz brain stimulation. Patients are randomly assigned to one of two groups: 40 Hz masked flickering white light (active) and continuous non-flickering white light matched in color temperature and brightness (placebo). This is a double-blind study, so neither the participant nor the researcher will know which treatment the participant is receiving. Both kinds of light appear as white light, so the normal white light serves as a well-matched placebo. As a precaution, the investigators doing the assessments will not see the devices turned on but will instruct the trial participants on correct device use during the baseline meeting. Each participant is handed out a user manual with detailed instructions on how to handle the light therapy and recommended daily usage times. Participants will receive in-person instructions and will be additionally contacted *via* phone to ensure a smooth process and proper implementation of the light therapy.

Participants take light therapy at home; however, the variability in the specific implementation details of the treatment, particularly among subjects with poor adherence, poses potential challenges to the trial’s overall outcome. To mitigate these concerns and enhance the integrity of the study, adherence to the treatment protocol in both groups is monitored using an eye-tracking system. This system documents each participant’s active usage time, ensuring a comprehensive assessment of treatment adherence.

A treatment blinding test will be administered to the participants at day 42. The treatment blinding test assesses the participant’s awareness of which treatment group, he/she was allocated to for assessment of blinding efficacy. In addition, an evaluation of participants’ expectations regarding the effectiveness of the treatment will be systematically conducted at the initial visit, serving as a baseline measure.

An independent investigator will program 30 active treatment and 30 placebo devices in total assigned with labels A and B to the device identification numbers. The statistician creates unequal randomization blocks (e.g. ABBA, BAABBA) where he assigns a patient number (e.g. FELIX01, FELIX02) to the treatment group (A or B) and then the treatment group to a random device (corresponding to the group). The block size is blinded to investigators.

The treatment period will last six weeks, and patients will come to their final follow-up visit at week 8 to assess any lasting antidepressant effects of light treatment. The study procedures include five visits with assessments using validated clinical scales administered by trained healthcare professionals, self-administered symptom, and quality of life scales. Additionally, neurocognitive evaluation and EEG procedures will be conducted (Figure 1).

